## Abstract

**Background:**

World Health Organization (WHO) recommends that the episiotomy rate should be around 10%, which is already a reality in many European countries. Currently the use of episiotomy should be restricted and physicians are encouraged to use their clinical judgment to decide when the procedure is necessary. There is no clinical evidence corroborating any indication of episiotomy, so until the present moment it is not yet known whether episiotomy is indeed necessary in any context of obstetric practice.

**Objectives:**

To compare maternal and perinatal outcomes in women undergoing a protocol of not performing episiotomy versus selective episiotomy.

**Methods/Design:**

An open label randomized clinical trial will be conducted including laboring women with term pregnancy, maximum dilation of 8 cm, live fetus in cephalic vertex presentation. Women with bleeding disorders of pregnancy, indication for caesarean section and those without capacity to consent and without legal guardians will be excluded. Primary outcomes will be frequency of episiotomy, delivery duration, frequency of spontaneous lacerations and perineal trauma, frequency of instrumental delivery, postpartum blood loss, need for perineal suturing, number of sutures, Apgar scores at one and five minutes, need for neonatal resuscitation and pH in cord blood. As secondary outcomes frequency complications of perineal suturing, postpartum perineal pain, maternal satisfaction, neonatal morbidity and admission newborn in NICU will be assessed. Women will be invited to participate and those who agree will sign the consent form and will be then assigned to a protocol of not conducting episiotomy (experimental group) or to a group that episiotomy is performed selectively according to the judgment of the provider of care delivery (control Group). The present study was approved by IMIP’s Research Ethics Committee.

**Trial Registration:**

Clinical Trials Register under the number and was registered in ClinicalTrials.gov under the number NCT02178111.

## Introduction

Despite all available evidence corroborating the selective use of episiotomy and the recommendation of NOT to perform routine episiotomies, questions remain about what are the real indications to perform episiotomy in modern obstetrical practice [1].

American College of Obstetricians and Gynecologists (ACOG) guidelines state that “the best available data do not support the liberal or routine use of episiotomy. However, there is a role for episiotomy for maternal or fetal indications such as avoiding severe maternal lacerations or to facilitate difficult births” [2]. The World Health Organization recommends an episiotomy rate of 10% as “a good goal to pursue” [3], based on the data obtained in the English randomized controlled trial published in 1984 [4].

In the Cochrane systematic review, a question arises: What would actually be the indications of episiotomy? Some situations are placed such as preterm delivery, breech delivery, macrosomia, shoulder dystocia, instrumental deliveries (forceps or vacuum extraction), non-reassuring fetal heart rate and rigid perineum or threat of severe perineal rupture [5]. However, these situations have been questioned as an indication of episiotomy and clearly this issue needs to be further studied in randomized clinical trials [1]. While it is clear that routine episiotomy should be avoided, there is no solid evidence corroborating ANY indication of episiotomy. The benefits of the use of episiotomy in these selected conditions remain controversial [6].

Recently, it has been suggested that episiotomy should never be performed. An original recommendation for performing episiotomy was famously summarized by Scott (2005) [7]: “Don’t just do something, sit there!”. In a study including 168,077 singleton vaginal deliveries in the Soroka University Medical Center, Israel (2012), mediolateral episiotomy was found to be an independent risk factor for 3rd or 4th degree perineal tears, even in critical conditions such as shoulder dystocia, instrumental deliveries, occiput-posterior position, fetal macrosomia, and non-reassuring fetal heart rate. The rates of episiotomy in this Hospital declined from more 30% in 90’s to less than 5% in 2010 [8].

With a protocol of not conducting combined with episiotomy perineal protection strategies, Amorim et al. found an intact perineum rate around 60% and only 23% of pregnant women in need of sutures that have not undergone episiotomy [9,10]. However, this was a non-controlled study with an isolated sample and the authors suggest the need for randomized clinical trials comparing a policy of not conducting episiotomy with the policy of selective episiotomy.

Reviewing the Medline, Lilacs/SciELO, EMBASE, Scopus, and the Cochrane Library databases using the keywords “episiotomy” and “vaginal delivery” in Portuguese, English and Spanish, with filters “randomized clinical trial” and “systematic review”, no clinical trial or clinical trial protocol addressing the non-performance of episiotomy care for vaginal delivery was found.

Thus, the present study will be conducted in order to compare maternal and perinatal outcomes in women undergoing a protocol of not conducting episiotomy vs. selective episiotomy.

### Objectives and hypothesis

The overall objective is to compare a protocol of not conducting episiotomy vs. selective episiotomy in a randomized clinical trial. The hypothesis is that never conducting a episiotomy is superior to using episiotomies in a selective manor.

#### ***Specific objectives***

*In pregnant women randomized to a protocol of not conducting an episiotomy vs. selective episiotomy*,*compare*:

### Primary maternal outcomes

• Duration of the second stage of labor;

• Frequency of episiotomy;

• Indication of episiotomy (imminent severe perineal rupture, instrumental delivery, shoulder dystocia, prolonged second stage of labor and non-reassuring fetal heart rate);

• Frequency of spontaneous lacerations;

• Frequency of instrumental delivery;

• Frequency of perineal trauma;

• Blood loss at delivery;

• Perineal need for suturing;

• Number of sutures;

### Primary perinatal outcomes

• Apgar scores at 1 and 5 minutes;

• Need for neonatal resuscitation;

• Cord blood pH at birth;

### Secondary maternal outcomes

• Frequency of severe perineal trauma;

• Perineal suturing complications;

• Perineal pain after childbirth;

• Maternal satisfaction;

### Secondary perinatal outcomes

• Neonatal morbidity

• Newborn admission to the NICU.

#### ***Main hypothesis***

In women randomized to a protocol of not conducting as episiotomy, in comparison to a selective episiotomy protocol:

• Duration of the second and frequency of spontaneous lacerations and perineal trauma is the same;

• Blood loss at delivery is lower, as is the need for suturing and also the number of sutures;

• Apgar scores at 1 and 5 minutes, need for neonatal resuscitation and cord blood pH at birth is the same in both groups.

• Frequency of severe perineal trauma, complications of perineal suturing, and perineal pain after childbirth is lower.

• Maternal satisfaction is higher.

• Neonatal morbidity and newborn admission to the NICU is similar.

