### Sample size calculation

The sample size was calculated on the Open Epi 2.3 (Atlanta, GA), with an expected rate of episiotomies in the protocol group of not conducting episiotomy of 1% versus a 10% rate of episiotomies in the group of episiotomy selective [3,4]. For a power of 80% and a confidence level of 95%, 200 women would be needed, a figure that has increased by 20% to compensate for eventual losses after randomization, so that 240 women will be randomized.

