### Data analysis plan

The data analysis will be performed using the public domain software Epi Info version 7.1.4 (Centers for Disease Control and Prevention, Atlanta, GA), or the newest available version under the intention to treat principle. The statistician will remain blind to the meaning of the Groups A or B to which patients are allocated until the tables and the analysis concluded. The approach for analysis will be that showed in Figure 1 using an intention-to-treat strategy and following the correspondent recommendations from the CONSORT statement [11]. The characteristics of the participants in each group will be compared with Student’s *t* test for continuous variables with normal distribution and Mann–Whitney U test for discrete and ordinal variables or those with non-normal distribution. Categorical variables will be compared with Pearson’s χ [2] test or Fisher’s exact test, as appropriate. P values for all tests will be two tailed at a 5% level of significance. Risk ratios and their 95% confidence intervals will be calculated as a measure of relative risk. The number needed to treat (NNT) and its 95% confidence interval will be calculated for the outcomes in which a beneficial effect of not performing an episiotomy is achieved, using the EBM calculator [http://moosenose.com/EBCalculator.htm]; in case of adverse effects the number needed to harm (NNH) and its 95% confidence will also be calculated.

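### The main hypothesis expects eight outcomes to be unchanged, but tests of no difference and intervals without a margin cannot show this

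*Protocol article*

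**What the plan says.** The protocol article, under Objectives and hypothesis, gives one overall claim: "The hypothesis is that never conducting a episiotomy is superior to using episiotomies in a selective manor". The Main hypothesis section then goes outcome by outcome. Blood loss, suturing, severe trauma, suturing complications and pain are expected to be lower, and satisfaction higher. The other outcomes listed there are expected not to change:

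- Maternal: "Duration of the second and frequency of spontaneous lacerations and perineal trauma is the same" (I read the first item as the second stage of labor).
- Perinatal, primary: "Apgar scores at 1 and 5 minutes, need for neonatal resuscitation and cord blood pH at birth is the same in both groups".
- Perinatal, secondary: "Neonatal morbidity and newborn admission to the NICU is similar".

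That makes eight outcomes, counting the two Apgar scores as one. Six of them stand in the lists of primary outcomes.

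The Data analysis plan names Student's t, Mann–Whitney, chi-square and Fisher tests, and adds: "P values for all tests will be two tailed at a 5% level of significance". It also states: "Risk ratios and their 95% confidence intervals will be calculated as a measure of relative risk", with NNT for benefits and NNH for adverse effects. The Sample size calculation rests on an "expected rate of episiotomies in the protocol group of not conducting episiotomy of 1% versus a 10% rate of episiotomies" in the selective group. The article states no margin for any outcome.

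**The concern.** A two-sided test of no difference can reject sameness but cannot establish it. A large p value may mean that the arms are alike, or that the trial was too small or too noisy to tell them apart. A risk ratio with its interval says more, but supports sameness only if someone has said how wide a departure still counts as unchanged.

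The unchanged outcomes carry the no-harm half of the trial's message: that leaving out episiotomy does not lengthen the second stage, add trauma or worsen the newborn's condition. The Discussion presents the study as evidence on the possible risks of never performing episiotomy, so this half is central. If nothing in the plan can support it, readers will tend to fall back on non-significance.

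**Working it through.** **The plan's own figure.** Inputs from the Sample size calculation: 1% versus 10%, two-sided 5%, 80% power. The allocation ratio is not stated; I assume 1:1. With pooled variance and no continuity correction:

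n per arm = [1.96·√(2·0.055·0.945) + 0.842·√(0.01·0.99 + 0.10·0.90)]² / 0.09² = (0.632 + 0.266)² / 0.0081 = 0.806 / 0.0081 ≈ 99.5, rounded up to 100.

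That is 200 in total, and 200 × 1.2 = 240. The stated figures are reproduced, as a calculation for showing a difference in episiotomy frequency. No outcome expected to be unchanged enters it.

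**Inputs for the unchanged outcomes.** I use 100 per arm (200 analysed) and 120 per arm (240 randomized). The 40% trauma rate is 100% minus the roughly 60% intact perineum that the Introduction reports from an earlier uncontrolled series. The article gives no neonatal rates; 5% is assumed, with 2% and 10% as a range.

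**Chance that a real rise is non-significant.** Power = Φ{[Δ − 1.96·√(2p̄(1−p̄)/n)] / √([p₁(1−p₁)+p₂(1−p₂)]/n)}. For 40% to 50% at n = 100: (0.10 − 1.96 × 0.0704)/0.0700 = −0.54, so power is 29% and the result is non-significant 71% of the time.

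| True rise | 100 per arm | 120 per arm |
|---|---|---|
| 40% to 50% | 71% | 66% |
| 40% to 55% | 43% | 36% |
| 2% to 4% (assumed) | 87% | 85% |
| 5% to 10% (assumed) | 73% | 69% |
| 10% to 15% (assumed) | 81% | 79% |
| 10% to 20% (assumed) | 49% | 42% |

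**Width of the intervals.** For a risk difference at 40% and 100 per arm, the half-width is 1.96·√(2·0.4·0.6/100) = 13.6 points; at 5% it is 6.0 points. On the planned risk-ratio scale, suppose the observed rates are exactly equal. At 40% the standard error of the log ratio is √(2·(0.6/0.4)/100) = 0.173, so the interval runs from 0.71 to 1.40. At 5% it is √(2·(0.95/0.05)/100) = 0.616, so the interval runs from 0.30 to 3.35.

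**Smallest margin the trial could support.** With equal true rates, 80% power and a 95% interval, the margin is (1.960 + 0.842)·√(2p(1−p)/n) for non-inferiority and (1.960 + 1.282)·√(2p(1−p)/n) for equivalence. At 40% and n = 100 these are 2.802 × 0.0693 = 19.4 points and 3.242 × 0.0693 = 22.5 points.

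| Rate | Non-inferiority, 100 (120) per arm | Equivalence, 100 (120) per arm |
|---|---|---|
| 40% | 19.4 (17.7) points | 22.5 (20.5) points |
| 10% (assumed) | 11.9 (10.9) points | 13.8 (12.6) points |
| 5% (assumed) | 8.6 (7.9) points | 10.0 (9.1) points |
| Continuous | 0.40 (0.36) SD | 0.46 (0.42) SD |

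Judging equivalence by a 90% interval instead gives 20.3 (18.5) points at 40%.

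**Numbers for a 10-point margin at 40%.** Non-inferiority: 2.802² × 0.48 / 0.10² ≈ 377 per arm. Equivalence: 3.242² × 0.48 / 0.10² ≈ 505 per arm. The 10 points are for illustration; the documents give no margin.

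**The case against.** - **The plan is not limited to p values.** Risk ratios with 95% intervals and NNH are planned, so the binary safety outcomes will have intervals. This stands: a reader might infer that the plan has nothing but significance tests, and that would be wrong. What is missing is a limit to judge the intervals against.
- **No rule says that p>0.05 confirms sameness.** This also stands. A reader might infer that the plan intends non-significance as proof of safety. Neither the Main hypothesis nor the Data analysis plan says so; it is a foreseeable misreading, not a stated rule.
- **Superiority and sameness need not conflict.** Better on some outcomes and unchanged on others is an ordinary meaning of superior overall. The two hypothesis sections can be read together, and I do not count them as a contradiction.
- **This is a condensed article.** Estimates for the continuous outcomes may well be in a fuller document, so their absence is no fault in itself. But the hypotheses and the tests are both fixed here, and they do not fit each other.
- **Larger harms would often be seen.** A rise from 40% to 55% is non-significant only 43% (36%) of the time, so it does not follow that any important harm would usually be missed. Rises of about 10 points, or an assumed neonatal doubling from 5%, usually would be.
- **The 40% is borrowed** from an uncontrolled series without episiotomy and is only a stand-in for the selective arm. The precision argument barely depends on it: at 50% the half-width is 13.9 points, at 20% it is 11.1.

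**Conclusion.** The concern holds as a mismatch between hypothesis and analysis. Eight outcomes, six of them primary, are predicted to be unchanged. The tests named cannot support that prediction, the planned intervals have no margin to be read against, and the trial was sized for a different question. At the planned size, non-significance would be the likely result even with a 10-point rise in trauma (71%, or 66% at 120 per arm) or an assumed neonatal rise from 5% to 10% (73%, or 69%). Only wide margins are within reach: at a 40% rate and 100 per arm, about 19 points for non-inferiority and about 22 for equivalence.

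These figures assume 1:1 allocation, the 40% rate derived from the earlier series, neonatal rates of my choosing and, for the margins, equal true rates with 80% power. The mismatch itself rests on none of them. Nor does it touch the comparison of episiotomy frequency, whose sample size reproduces.

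**What to change.** In Main hypothesis, replace the predictions of sameness and similarity with estimation: for each of these outcomes, the effect estimate and its 95% confidence interval will be reported. In the Data analysis plan:

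1. Judge these outcomes on the interval: the risk ratio already planned for binary outcomes, and a mean or Hodges–Lehmann difference for the continuous ones, such as second-stage duration and cord pH.
2. State that p>0.05 is not evidence of sameness.
3. State that absence of harm will be concluded only if the interval excludes a margin set before unblinding, and that the result is otherwise inconclusive. The margin is a clinical choice for the investigators; it should be on the same scale as the reported effect.

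The cost is wording and a few extra intervals, with no additional patients. The downside is that at 200 to 240 women the safety outcomes, above all the neonatal ones, may have to be reported as inconclusive.

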## Methods/design

### Study design

The present study is an open label randomized controlled trial.

### Study population and location

The study population will comprehend all women in labor hospitalized in IMIP during the data collection period.

### Eligibility criteria

Laboring women with term pregnancy, maximum dilation of 8 cm, live fetus in cephalic vertex presentation will be included and women with bleeding disorders of pregnancy, immediate indication for caesarean section and women without capacity to consent and without legal guardians will be excluded.

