### Procedures for selecting participants and randomization

Eligible patients will be invited to participate and those who agree will be included in the study and then will be allocated to either a protocol of not conducting an episiotomy or a protocol of selective episiotomy, according to a random list of numbers generated by the Random Allocation Software Ispharan Iran, version 1.0. This list of randomization will be provided by the statistician to researcher who will be responsible for preparing the envelopes containing instructions regarding which group the patient is allocated to (A: Intervention= > not to use episiotomy or B: Control= > selective episiotomy). This procedure will be followed in order to guarantee the concealment of allocation of patients in both arms. Patients and medical staff will not be blind to the intervention condition, but the researcher and the statistician performing the analysis will be blinded to the meaning of the letters A or B to which participants will be allocated.

During the observation period the birth attendants will conduct delivery of baby and placenta according to routine practice, except for the instruction about the use of episiotomy. Birth attendants will collect, using special plastic bags, blood loss after delivery and the amount will be registered. Blood from the cord will be collected to perform pH analysis, and suture of any lacerations that may occur will be performed according to their clinical judgment. After 24 hours of delivery, women will be interviewed and perineal pain will be evaluated using a visual pain scale and women’s satisfaction will also be assessed. During the observation period, if before birth occurs, there is an indication of cesarean delivery, the women will be excluded from the study.

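### Women allocated at 8 cm dilation or less are excluded if a caesarean is later indicated, which conflicts with intention to treat; all should be analysed, and opening the envelope at full dilation would reduce their number

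*Protocol article*

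**What the plan says.** All of this is in the protocol article.

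- **Eligibility criteria.** Women in labour at term may enter at a "maximum dilation of 8 cm". The only caesarean screen at entry is an "immediate indication for caesarean section".
- **Procedures for selecting participants and randomization.** Of eligible women, "those who agree will be included in the study and then will be allocated" by envelope. No later moment for opening the envelope is described. Attendants are to "conduct delivery of baby and placenta according to routine practice, except for the instruction about the use of episiotomy". The section states that "Patients and medical staff will not be blind to the intervention condition". It then says that "if before birth occurs, there is an indication of cesarean delivery, the women will be excluded from the study".
- **Sample size calculation.** 200 women are needed for 1% versus 10% episiotomy, a figure "increased by 20% to compensate for eventual losses after randomization", giving 240.
- **Data analysis plan.** The analysis is to follow intention to treat, with two-sided tests at 5%, and chi-square or Fisher's exact test as appropriate for categorical variables.

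**The concern.** The exclusion acts between allocation and birth, and it is triggered by a decision of staff who know the arm. If knowing that episiotomy is, or is not, available influences even a few decisions for caesarean, the women left in the two arms are no longer comparable. Every maternal and perinatal outcome is then compared in a selected set. An analysis without these women is not by intention to treat, whatever it is called.

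The timing makes the problem larger than it needs to be. The arms differ only in an instruction used at delivery, yet the text has women allocated during the first stage. Every caesarean indicated between that point and full dilation therefore falls after randomisation, although the allocation had not yet had any use.

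**Working it through.** **Step 1. Set the statements side by side.** The order is inclusion at 8 cm or less, allocation, open-label care, a possible caesarean indication, exclusion. The exclusion is placed in the observation period before birth, and the sample size section itself expects losses after randomisation. The Data analysis plan promises intention to treat. The exclusion and the promise cannot both be applied.

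**Step 2. Reproduce the sample size.** Inputs from the article: p1 = 0.01, p2 = 0.10, two-sided 5%, power 80%. A 1:1 ratio is assumed.

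n per arm = [1.960 × √(2 × 0.055 × 0.945) + 0.842 × √(0.01 × 0.99 + 0.10 × 0.90)]² / 0.09²
= (0.632 + 0.266)² / 0.0081 = 99.5, so 100 per arm and 200 in all, as stated.

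200 × 1.20 = 240. The allowance is 40/240 = 16.7% of those randomised.

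**Step 3. Power if caesareans are kept or excluded.** The article gives no caesarean rate, so the share c is assumed. A woman delivered by caesarean cannot have an episiotomy.
- Kept: 120 per arm, rates 0.01(1−c) and 0.10(1−c).
- Excluded: 120(1−c) per arm, rates 0.01 and 0.10.

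Power is by exact binomial enumeration. The first figure is chi-square alone. The second is chi-square with Fisher when an expected count is below 5, which is one reading of the planned test choice.

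| c | Kept | Excluded |
|---|---|---|
| 0% | 91.9% / 90.0% | same |
| 10% | 88.3% / 84.7% | 108 per arm: 88.3% / 84.8% |
| 16.7% | 85.2% / 80.1% | 100 per arm: 85.4% / 80.3% |
| 20% | 83.5% / 77.3% | 96 per arm: 83.7% / 77.6% |
| 30% | 77.5% / 67.5% | 84 per arm: 77.7% / 67.8% |

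Keeping rather than excluding changes power by at most 0.3 points. What matters for power is the number of vaginal births.

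**Step 4. Power if the envelope is opened at full dilation and all randomised women are kept.** Let f be the share of caesareans indicated before full dilation, also not in the article. The caesarean share among those randomised becomes c(1−f)/(1−cf). For c = 20%:

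| f | Share after allocation | Chi-square alone | With Fisher for small counts |
|---|---|---|---|
| envelope at inclusion | 20.0% | 83.5% | 77.3% |
| 50% | 0.10/0.90 = 11.1% | 87.8% | 84.0% |
| 70% | 0.06/0.86 = 7.0% | 89.5% | 86.5% |
| 90% | 0.02/0.82 = 2.4% | 91.1% | 88.9% |

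**Step 5. Where the gain comes from.** To randomise 240 at full dilation, 240/(1−cf) women must be consented: 240/0.90 = 267, 240/0.86 = 280 or 240/0.82 = 293 for f = 50%, 70% or 90%, before any loss of fast births. At f = 50%, late opening gives 240 × 0.889 = 213 vaginal births. Randomising 267 at inclusion gives 267 × 0.80 = 214. The gain per randomised woman is bought with extra consents.

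**Step 6. Fit with the outcomes.** Under Main outcomes, the second-stage clock starts at full dilation with pushing. Opening the envelope at confirmed full dilation is compatible with that clock, provided that it does not hold up care.

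**The case against.** The strongest case against changing the timing has four parts.

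- **It leaves the bias that matters most.** The situations listed for selective episiotomy arise at or near birth, so knowledge of the arm is most likely to sway a caesarean decision in the second stage. Those caesareans still follow allocation. First-stage caesareans should be largely unrelated to arm. This stands, and it is why deleting the exclusion comes first and the timing is only an addition.
- **The loss is budgeted.** At 16.7% loss, power is 80% with the Fisher rule and 85% with chi-square alone. This also stands. The allowance replaces numbers, however, and does not repair a comparison from which women were removed with the arm known.
- **The timing is inferred.** The article gives only an order, no moment for opening the envelope, and Figure 1 is not shown. One should not say that women are allocated the instant they consent. The order as written still puts the exclusion after allocation.
- **Late opening narrows the population** and places a trial step at the start of the second stage, whose duration is a primary outcome. This is a real but modest cost.

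A reader might also infer that late opening would avoid most of the losses. That requires more than half of the caesareans to be indicated before full dilation, and the documents do not say so. A reader might infer that keeping caesareans under intention to treat costs power by dilution. Step 3 shows that it costs almost nothing compared with excluding them.

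**Conclusion.** The conflict is real: the plan excludes women after open-label allocation while promising intention to treat. It should be corrected whatever the caesarean rate, because the harm is possible bias, whose size cannot be computed from the documents.

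The change in timing is worthwhile but secondary. At an assumed 20% caesarean share with all women kept, it raises power by about 7 to 12 points with the Fisher rule (77.3% to between 84.0% and 88.9%) or about 4 to 8 points with chi-square alone (83.5% to between 87.8% and 91.1%), for f from 50% to 90%. Both c and f are assumptions.

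Two readings go too far. The documents do not show that the trial is underpowered: power falls below 80% only if the loss exceeds about 16.7% with the Fisher rule, and with chi-square alone it is still 83.5% at 20% and below 80% at 30%. Nor is the 8 cm limit an error. It can stay as the limit for consent.

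**What to change.** 1. In Procedures for selecting participants and randomization, delete the exclusion of women with a later caesarean indication. State that every randomised woman is analysed in her allocated arm, and report caesareans by arm. This costs a sentence, plus a rule for recording delivery outcomes, such as second-stage duration, in women delivered by caesarean.
2. As an addition, keep eligibility and consent at 8 cm or less, but state that the next envelope is opened only when full dilation is confirmed and no caesarean is indicated. Define the randomised population from that moment, and keep later caesareans in the analysis.
3. Restate what the 40-woman allowance covers once caesareans are no longer exclusions, and give the caesarean share that is assumed.

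The second change needs envelopes at the place of birth and more consents: about 267 to 293 for 240 randomised under the assumptions above. Some very fast births will not be randomised. As they drop out before allocation, this slightly narrows the population but does not bias the comparison.
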